## **4.2 Exclusion Criteria**

Patients will be excluded if they have:

- Serious heart, liver, lung, or kidney diseases;
- Syphilis or AIDS;
- Severe digestive disease or malnutrition;
- Severe primary hematological disorders;
- Received other treatment that may affect the efficacy evaluation of the present intervention;
- Infection, inflammation, scar, or injury close to the site of the selected acupoints;
- Pregnancy, or plans for pregnancy;
- Had a history of mental illness other than drug dependence.

In addition, all patients are instructed not to take any other medications aiming at alleviating withdrawal symptoms, improving sleep quality, or managing depression and anxiety during the study, in order to avoid initiating other interventions. Patients who consume such medications are excluded from the study.

## **4.3 Recruitment**

All patients will be recruited in the outpatient clinics of the participating hospitals by local advertising, hospital website, and hospital WeChat Public Accounts.

## **5. Intervention**

Acupuncture treatment will be performed by licensed acupuncturists who has at least 3 years of acupuncture experience. All participants will receive 24 sessions of

30-minutes acupuncture over 8 weeks. We set up the standardized ritual operations and perform them in both manual acupuncture and sham control group.

### **5.1 Manual Acupuncture Group**

Manual acupuncture will be applied at acupoints that belong to Jin's three-needle acupuncture (JTN). JTN is a clinical acupuncture school which has been successfully applied in several RCTs [45,46]. This school always combines three acupoints that have a synergistic effect as an acupoints group. Among them, we will choose "Dingshen-zhen", "Sishen-zhen" and "Shouzhi-zhen" which are commonly used to treat psychiatric disorders such as opiate withdrawal [47]. The location of these points is described in **Table 1** and **Figure 2**.

Sterile stainless-steel disposable acupuncture needles (Huatuo, Suzhou, China; lengths and diameters: 25 mm × 0.3 mm) will be used in this group. Among the chosen points, Shouzhi-zhen will be needled at an angle of 45-90° to the participant's skin, while Dingshen-zhen and Sishen-zhen will be needled at an angle of 15-30° to the skin. The needles will be inserted at a depth of 5-30 mm. Then, the needles will be manually stimulated to achieve the typical acupuncture sensation of "de qi" which is characterized as soreness, numbness, and heaviness. Over a 30-minute period, manual manipulation for each acupoint lasts 10 seconds and is repeated three times with intervals of 10 minutes.

**Table 1** Acupoints used in the manual acupuncture group

| Acupoints                                           | Location                                                                                                                                                                                 | Depth of insertion |
|-----------------------------------------------------|------------------------------------------------------------------------------------------------------------------------------------------------------------------------------------------|--------------------|
| Sishen-I
(GV21: Qianding)                 | On the head, 3.5B-cun superior to the anterior hairline, on the anterior median line.                                                                                                    | 0.5-0.8 cun        |
| Sishen-II
(GV19: Houding)                 | On the head, 5.5B-cun superior to the posterior hairline, on the posterior median line.                                                                                                  | 0.5-0.8 cun        |
| Sishen-III                                   | On the head, 1.5 cun left lateral to the anterior median line and at the same level as GV20. GV20 is on the head, 5B-cun superior to the anterior hairline, on the anterior median line. | 0.5-0.8 cun        |
| Sishen-IV                                    | On the head, 1.5 cun right lateral to the anterior median line and at the same level as GV20.                                                                                            | 0.5-0.8 cun        |
| Dingshen-I                                   | On the head, directly 0.5 cun superior to EX-HN3. EX-HN3 is on the head, between the right medial end of the eyebrow and the left one.                                                   | 0.5-0.8 cun        |
| Dingshen-II                                  | On the head, directly 0.5 cun superior to left GB14. GB14 is on the head, 1B-cun superior to the eyebrow, directly superior to the centre of the pupil.                                  | 0.5-0.8 cun        |
| Dingshen-III                                 | On the head, directly 0.5 cun superior to right GB14                                                                                                                                     | 0.5-0.8 cun        |
| Shouzhi-I
(bilateral)
(HT7: Shenmen)   | On the anteromedial aspect of the wrist, radial to the flexor carpi ulnaris tendon, on the palmar wrist crease.                                                                          | 0.5-0.8 cun        |
| Shouzhi-II
(bilateral)
(PC6: Neiguan)  | On the anterior aspect of the forearm, between the tendons of the palmaris longus and the flexor carpi radialis, 2B-cun proximal to the palmar wrist crease.                             | 0.8-1.0 cun        |
| Shouzhi-III
(bilateral)
(PC8: Laogong) | On the palm of the hand, in the depression between the second and third metacarpal bones, proximal to the metacarpophalangeal joints.                                                    | 0.5-0.8 cun        |

Note: The prescribed acupoints come from the WHO Standard Acupuncture Point Locations in the Western Pacific Region. The “*Shouzhi-I*”, “*Shouzhi-II*”, “*Shouzhi-III*” only needles one hand each time, and both sides take turns for treatment.

[figure not shown]

Figure 2 Acupoints used in the manual acupuncture group (The lower right corner shows only the right hand acupoints)

## 5.2 Sham Control Group

Non-penetrating sham acupuncture will be applied at the same acupoints as the

manual acupuncture group. Sterile stainless-steel disposable blunt acupuncture needles (Huatuo, Suzhou, China; lengths and diameters: 25 mm × 0.3 mm) are used as sham needles. When they are fixed on the skin through acupuncture auxiliary device, patients felt a pricking sensation, simulating a puncture of the skin. However, the needles do not penetrate the skin when they are pressed by acupuncturists.

Patient-blinded acupuncture intervention uses a special acupuncture auxiliary device (**Figure 3**). The device has already been granted a patent by China's national intellectual property administration (No. ZL 202223328917.3). The device consists of a plastic pedestal and a guide tube, and the shape of the device used is the same in both groups. For real acupuncture, we use hollow instruments where needles can be inserted hygienically directly into the skin. For placebo acupuncture, we use non-hollow instruments and blunt needles. To achieve a single-blind outcome, the acupuncturist fixes an acupuncture auxiliary and a needle or placebo needle to the skin of the acupoint after sterilization. Then the acupuncturist quickly taps the top of the tube to make the needle go downward and removes the tube. Therefore, participants are blinded to group and intervention by entering the needle through this acupuncture auxiliary device.

[figure not shown]

Figure 3 acupuncture auxiliary device (A: hollow instruments for real acupuncture. B: non-hollow instruments for placebo acupuncture)

## **6. Outcome**

### **6.1 Primary Outcomes**

#### **6.1.1 The Rate of Methadone Dose Reduction**

One primary outcome is the rate of methadone dose reduction, defined as the proportion of participants who achieve a reduction in methadone dose of  $\geq 20\%$  compared to baseline after 8 weeks of intervention. Based on the results of previous studies and the standards and clinical guidelines of MMT in the United States and Canada, we find that achieving a reduction in methadone dose of  $\geq 20\%$  at the end of intervention is associated with significant clinical benefits[40,41,48,49]. Therefore, a 20% reduction in methadone dose is used as the threshold to define significant improvement in tapering effectiveness.

Enrolled patients come to visit the clinic every day to take methadone, which is strictly administered by the physicians as required by the MMT clinics. Daily consumption of methadone from baseline to the 20th week will be obtained from physicians and recorded by independent research assistants, which is used to calculate average daily methadone dose per week and the rate of methadone dose reduction.

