#### **3.2 Randomization, Allocation, and Blinding**

Eligible patients are randomly assigned in an equal ratio to the manual acupuncture group or the sham control group via a central randomization system designed by the Clinical Research and Big Data Laboratory, South China Research Center for Acupuncture and Moxibustion, Guangzhou University of Chinese Medicine (<http://47.119.117.255/>). The randomization sequence is generated in the block size of 4. Participants will be informed that they have an equal chance to be assigned to the manual acupuncture group or the sham control group. After participants sign the informed consent form and complete baseline assessments, the researcher applies for the randomization number and allocates participants to each group. Allocation of participants is performed by an independent researcher at the clinical site who is not involved in the outcome assessment. Due to the nature of this study, acupuncturists are not blinded to group allocation. However, the outcome assessors, physicians who prescribe patient's methadone, national government personnel who is responsible for recording daily consumption of methadone, data collectors, and statisticians are all blinded to group allocations. Besides, an independent researcher supervises the conversation between acupuncturists and physicians to avoid them communicating issues related to the allocation. Upon the culmination of 8 weeks intervention, patients will be asked to guess whether they perceived the insertion of the needle tip into their skin to assess the efficacy of blinding maintenance.

[figure not shown]

Figure 1: Flowchart of trial procedures

\*A: Daily Consumption of Methadone; B: Visual Analog Scale (VAS) for opioid craving;  
C: Clinical Opioid Withdrawal Scale (COWS); D: Beck Anxiety Inventory (BAI); E: Beck Depression Inventory II (BDI-II); F: Pittsburgh sleep quality index (PSQI)

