## **7. Urine Test**

All participants will be asked to submit a urine sample at baseline, and randomly during the study each month, which are used to test for opioid use.

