## 11. Statistical Analysis

Statistical analysis will be performed by the Clinical Research and Big Data Laboratory, South China Research Center for Acupuncture and Moxibustion, Guangzhou University of Chinese Medicine. The statistician will be blinded to group allocation until final unblinding. SAS 9.4 will be utilized for data analysis. Missing data are filled by using multiple imputation.

Continuous variables are reported as the mean with standard deviation or median and interquartile range. Categorical variables are described as numbers and percentages using  $\chi^2$  test or Fisher's exact test. Longitudinal measures through 20 weeks (8 weeks of intervention and 12 weeks of follow-up) are analyzed for all outcomes. The analysis of proportion of participants with at least 20% reduction from baseline in the amount of methadone dose is performed using a generalized linear mixed-model. For opioid craving VAS and all secondary outcomes, analysis is conducted utilizing a linear mixed-model. For above models, values measured at baseline are used as covariates; intervention assignment, visit and intervention  $\times$  visit interaction are as fixed effects; and treatment centre and centre  $\times$  intervention interaction are as random effects. We assessed the poolability of treatment effects across centres by including centre  $\times$  intervention interaction in the model. If *P*-values corresponding to the centre  $\times$  intervention interaction term for both primary endpoints are greater than 0.10, the treatment effect is homogenous across centres [59].

Dynamic data will be demonstrated on the reduction in the methadone consumption and the opioid craving VAS score in the figures, separated by the manual acupuncture and sham group. Each row in the figures represents the reduction dose of

the daily consumption of methadone (the opioid craving VAS score) for one participant. Individuals who discontinue participation early appear at the bottom of each plot, whereas those with complete data appear at the top.

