## **Appendix 2: General principles for dosing determination of methadone maintenance treatment**

Methadone dosing in methadone maintenance treatment should be individually assessed and administered by the clinic physician based on the characteristics of the patient, taking into account factors such as the patient's physical condition, severity of drug dependence, and treatment outcome. All doses are dispensed under the direct observation of the clinic nurse and no doses are taken home.

Here are the general principles of methadone dosing in methadone maintenance treatment:

**Initial Dose:** The initial dose of methadone should be adequate to block cravings for other opioids and alleviate withdrawal symptoms. The starting dose typically ranges from 30 to 40 milligrams per day, depending on individual patient characteristics.

**Dose Adjustment:** After the initial dose, the methadone dose should be gradually adjusted based on the patient's response and needs. In general, the methadone dose is increased by 10 mg every 2 days, and as long as there are no complaints of sedation or side effects, the target dose is 60-120 mg per day.

**Dose Stability:** Once the patient's dose reaches a stable level that effectively controls withdrawal symptoms and cravings, clinic physician should maintain that dose while monitoring treatment efficacy and safety.

**Dose reduction:** methadone dose reduction should be provided when patient on dose stability stage requests a dose reduction. The rate of reduction is generally no more than 5% every two weeks. The clinic physician should closely monitor the patient's response. If adverse reactions occur, stop the methadone dose reduction process and, if necessary, return the methadone dose to the pre-tapering level.

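### The plan does not say how a missed dosing day enters the weekly methadone average; scored as 0 mg, two missed days make a patient who has not tapered a responder

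*Combined protocol and SAP*

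**What the plan says.** Protocol 6.1.1 and SAP 5.1 define the dose responder by a 20% threshold at the end of the eight-week intervention. Protocol 6.1.1 takes the data from daily consumption records, "which is used to calculate average daily methadone dose per week and the rate of methadone dose reduction". Protocol 3.2 also describes the record as consumption: it refers to "national government personnel who is responsible for recording daily consumption of methadone".

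Attendance is meant to be daily: "Enrolled patients come to visit the clinic every day to take methadone". Appendix 2 adds: "All doses are dispensed under the direct observation of the clinic nurse and no doses are taken home".

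Neither document gives the denominator of the weekly average (seven days or days dosed), the value assigned to a missed day, a minimum number of recorded days, or the days that form the baseline and week-8 windows. SAP 7.2 imputes missing outcomes under a missing-at-random (MAR) assumption, but does not say when a dose value is missing.

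On urine, Protocol 7 states: "All participants will be asked to submit a urine sample at baseline, and randomly during the study each month". SAP 5.2 lists the urine test as a secondary outcome; it is not part of the responder definition. Protocol 11 says: "For opioid craving VAS and all secondary outcomes, analysis is conducted utilizing a linear mixed-model". SAP 7.4 repeats this.

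**The concern.** Consumption and prescribed dose are the same only when the patient attends. With observed dosing and no take-home supply, the literal consumption on a missed day is zero. A weekly average that includes the zero falls although nobody has reduced the dose. Two statisticians could follow this plan and classify the same patient differently on a primary outcome.

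The error need not cancel. Equal absence in both arms pulls the rates together and costs power. Unequal absence moves the estimated effect in either direction. Patients who leave methadone maintenance treatment (MMT) before week 8 raise the same question in sharper form, because they have no dosed days to average.

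**Working it through.** **1. The plan's own figure.** Protocol 10 assumes 70% vs 36% responders, 5% two-sided significance and 90% power, and states 42 per group.

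- Unpooled formula: (1.960 + 1.282)² × (0.70×0.30 + 0.36×0.64) / 0.34² = 10.51 × 0.4404 / 0.1156, which rounds up to 41. The pooled formula gives 44.
- Power at 42 per group is 89%, and 42 / 0.85 rounds up to 50.

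The stated figures are therefore reproduced closely enough, and 70% vs 36% serves as the reference.

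**2. Effect of missed days scored 0 mg over seven days.** Let r be the true dose reduction, and m0 and m8 the missed days in the baseline and week-8 windows. Then

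apparent reduction = 1 − (1 − r) × (7 − m8) / (7 − m0).

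With m0 = 0:

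| m8 | Apparent fall if r = 0 | True cut needed to reach 20%: 1 − 0.8×7/(7 − m8) |
|---|---|---|
| 0 | 0% | 20% |
| 1 | 1/7 = 14.3% | 6.7% |
| 2 | 2/7 = 28.6% | none (−12%) |
| 3 | 3/7 = 42.9% | none |

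With m8 = 0 and absences at baseline, the bias reverses. One missed baseline day means that a true cut of 1 − 0.8×6/7 = 31.4% is needed; two mean 1 − 0.8×5/7 = 42.9%.

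Averaging only over days dosed gives r itself, however many days are missed.

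**3. Why small shifts matter here.** Appendix 2 describes a usual ceiling of 5% per two weeks. Four such steps give 4 × 5% = 20.0% of the starting dose, or 1 − 0.95⁴ = 18.5% if compounded. On that pace, patients finish at or just under the threshold, where one absence could decide their status. The sponsor should reconcile Appendix 2 with the threshold in Protocol 6.1.1; nothing here says which should change.

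**4. Size, same absence pattern in both arms.** The documents give no attendance figures, so this step rests on assumption. Let q be the share of true non-responders reclassified. The observed rate is p + (1 − p)q.

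| q | Acupuncture | Sham | Difference | Power at 42 per group, 5% level | Power at 42 per group, 2.5% level |
|---|---|---|---|---|---|
| 0 | 70.0% | 36.0% | 34.0 | 89% | 83% |
| 5% | 71.5% | 39.2% | 32.3 | 86% | 78% |
| 10% | 73.0% | 42.4% | 30.6 | 82% | 73% |
| 20% | 76.0% | 48.8% | 27.2 | 74% | 64% |

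Both levels are shown because Protocol 10 sizes the trial at 5% while SAP 7.4 tests primary outcomes at 2.5%.

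For scale, if each day is missed independently with probability 5%, 10% or 15%, the chance of two or more absences in seven days is 4.4%, 15.0% or 28.3%.

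**5. Size, unequal absence (assumed).**

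- q = 10% in sham only: 70.0% vs 42.4%. The difference falls by 0.64 × 0.10 = 6.4 points, against acupuncture.
- q = 10% in acupuncture only: 73.0% vs 36.0%. The difference rises by 0.30 × 0.10 = 3.0 points, in its favour.
- No true effect (36% in both arms), q = 20% vs 5%: a spurious difference of 0.64 × (0.20 − 0.05) = 9.6 points, in favour of the arm that misses more days.

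**6. Urine.** SAP 5.2 makes the urine test a secondary outcome, and SAP 7.4 sends every secondary outcome to a linear mixed model. A positive/negative result is therefore assigned to a model for continuous data.

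**The case against.** The strongest reply is that the plan never says a missed day is 0 mg. An average over days dosed fits the wording of Protocol 6.1.1 equally well and removes the effect. Patients are expected every day, so absences may be few. A patient who leaves may be treated as missing and imputed under SAP 7.2, not scored as zero. All of this stands. A reader might infer that the plan counts missed visits, relapse or departure from MMT as success, but the documents neither state nor exclude 0 mg scoring. The step from relapse to missed visits is plausible inference; no section states it.

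Nor do the documents support reading this as a bias towards acupuncture. Equal absence dilutes the difference, baseline absences work the other way, and the direction under unequal absence depends on which arm misses more.

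It can also be said that leaving urine out of the responder rule is a legitimate choice. The SAP hypothesis names dose and craving, craving is the other primary outcome, and urine is reported separately. That stands too, so a urine-based responder belongs only in a supportive analysis.

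What remains is the gap itself. Zero is the literal value of consumption on a day not attended, and imputation does not close the gap while the plan fails to say when a dose is missing. Because SAP 7.2 imputes from earlier measurements, a patient who had begun to taper and then left could be imputed as a responder.

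**Conclusion.** The concern holds as a gap in the definition of a primary outcome. The arithmetic on missed days is exact once 0 mg over seven days is assumed: two absences in the assessment week produce a responder without any taper, and one lowers the true cut required from 20% to 6.7%. Whether that scoring will be used cannot be settled from the documents.

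The trial-level sizes are illustrations and depend wholly on the assumed share reclassified. They run from a loss of 1.7 to 6.8 points off the 34-point difference when absence is equal, to shifts of 6.4 points against or 3.0 points for acupuncture at 10% in one arm only. The gap should be closed before unblinding, because afterwards the choice of denominator could be made with the result in view.

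The linear mixed model for urine is a separate and smaller error of specification. It follows directly from SAP 5.2 read with SAP 7.4.

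**What to change.** In Protocol 6.1.1 and SAP 5.1, compute baseline and week-8 dose as the mean over days on which a dose was taken. State a seven-day window for each and a minimum number of dosed days, and say that a window below the minimum is missing. Report days absent by arm and window.

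Add to SAP 7.5:

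- **Leavers.** A sensitivity analysis that scores participants who left MMT before week 8 as non-responders unless a completed taper is documented, alongside the MAR imputation of SAP 7.2. The exception is needed because Protocol 2.1.2 describes complete cessation as a goal of tapering.
- **Urine.** A supportive, not primary, analysis of a 20% or greater reduction with no urine test positive for non-methadone opioids in weeks 1–8. Methadone must be set aside explicitly, since Protocol 2.1.1 lists it as an opioid. With monthly sampling this is only a coarse check.

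In SAP 7.4, analyse the urine result with the binary generalized linear mixed model already planned for the dose responder; SAP 7.8 already names the procedure.

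The cost is definition text and a little more analysis. Daily consumption and urine results are already to be collected. Prescribed dose is not shown to be recorded, so the fix does not rely on it. Two points need confirming: that the records tell an absent day from a day with no entry, and that the urine assay separates methadone from other opioids. Responder rates may come out lower.
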